### Study design

Fig 2 provides a comprehensive overview of the entire study design and protocol. In a single-blind crossover study, every participant is given four different treatment conditions (INP/PL, INI/PL, INP/OLA, or INI/OLA) on two separate occasions. This means that each treatment is administered once during each menstrual cycle phase, resulting in participants receiving all conditions twice over the course of the study. All participants will receive oral PL at visit 1 and oral OLA at visit 2 of each cycle phase. Study visits will take place 2–6 weeks apart to ensure specific menstrual phase across the four visits and adequate washout between conditions. Participants will undergo two visits during the follicular phase of the menstrual cycle. To ensure a regular menstrual cycle, participants will be asked to provide information about the length of their last three cycles. Average cycle duration will be calculated to determine cycle phases. One cycle duration is defined as from cycle onset date (Day 1) to the day before the next cycle onset (i.e., Day 1 is defined as the first day of menstruation). Based on this, participants will be invited to complete the visits during the specific windows of their follicular and luteal phase. Menstrual cycle phases will be identified using calendar-based counting. The onset of their menstruation will be considered as the first day of the current menstrual cycle and will be denoted the start of the follicular phase. The follicular phase visit can take place starting 2 days after the start of the current menstrual cycle and no more than 17 days apart from the start of the subsequent cycle (i.e., they will be scanned between days 3 and 11 of their cycle). The luteal phase will be defined in the time frame of a maximum of 10 days but no less than 3 days before the start of the subsequent cycle (i.e., between day 18–25). Measurement of serum sex hormones (progesterone, estrogen, luteinizing hormone (LH) and follicular stimulating hormone (FSH)) will be done at each visit to confirm cycle phase.

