**Fig 2 pone.0352262.g002:**
[figure not shown]
Summary of overall study design and visit protocol. Following screening, eligible participants will be enrolled to take part in the 2x2 crossover study. Each participant will undergo a total of four primary study visits, two per cycle phase (follicular and luteal). Participants will receive oral placebo (PL) on days 0 and 1 of the first visit of each phase, and oral olanzapine (OLA) on days 0 and 1 of the second visit of each phase. At each visit, intranasal placebo (INP) will be administered prior to scan #1, and intranasal insulin (INI) prior to scan #2. Figure created on BioRender.com.

Each of the study periods will involve a three-day protocol (Fig 2): administration of OLA 5 mg (or PL) HS on day 0, OLA 10 mg (or PL) HS on day 1, and cognitive testing and MRI scanning on day 2. There will be two MRI scans on day 2, the first following administration of INP and the second following 160 IU of INI. Administration of INP always precedes INI as the effect of insulin in the brain is known to last for 2 hours, and counterbalancing the administration of INI first will require a much longer washout period/study visit, adding participant burden.

The two acute OLA doses of 5 mg and 10 mg are chosen for reasons of practicality and safety in line with previous studies [24,39]. The INI dose is the maximum safest dose that has been administered in humans and is chosen based on earlier work in nine healthy males showing a dose-dependent relationship on regional brain activity, with the strongest effects being observed after 160 IU [27]. This dose has been shown to induce changes in the brain in females as well [40,41]. Blood samples will be drawn before and after the MRI to measure insulin spillover. Dose-dependent spillover of INI into peripheral circulation has been reported, although the observed brain responses were not correlated with this transient rise in circulating insulin [27]. OLA levels will be measured to assess adherence.

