### Statistical analysis

The primary outcome is rsFC. Given the exploratory nature of this study, a formal power calculation was not performed. The sample size (N = 15) was instead informed by prior neuroimaging studies examining the effects of INI on MRI-derived outcomes, which have which have typically included 9–25 participants and reported large effect sizes (Cohen’s d: 0.8 to 1.4, f: 0.4–0.6). In the context of a within-subject crossover design, which reduces between-subject variability and increases statistical efficiency, this sample size is expected to provide adequate sensitivity to detect moderate-to-large effects in resting-state functional connectivity.

To address hypothesis #1, which is the difference in brain insulin sensitivity between cycle phases, analyses will be restricted to visits in which participants receive the oral PL. A linear mixed effects model will be conducted with rsFC as the dependent variable and fixed effects for intranasal condition (i.e., INI vs. INP), menstrual phase (follicular vs. luteal), and their interaction. Participant will be included as a random intercept, with age and BMI entered as covariates. The primary effect of interest is the intranasal condition x menstrual phase interaction, which tests whether the effect of INI (relative to INP) differs between follicular and luteal phases. Planned simple effects will assess (i) the effect of INI vs. INP within each phase, and (ii) the difference in INI-induced change (INI – INP) between phases.

To test the effect of OLA within each phase, a second linear mixed effects model will be conducted including all visits. Fixed effects will include intranasal condition (INI vs. INP), oral condition (OLA vs. PL), menstrual phase (follicular vs. luteal) and all interaction terms. Participants will be modeled as a random intercept, with age and BMI as covariates. The primary term of interest is the intranasal condition x oral condition x menstrual phase interaction, which tests whether OLA modifies INI-induced effects differently across cycle phases.

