The primary analysis will be conducted according to the intention-to-treat (ITT) principle, including all participants enrolled in the study who have completed at least one study visit. This analysis will account for missing data under the missing at random (MAR) assumption using the maximum likelihood estimation within the linear mixed model’s framework. A per-protocol analysis will also be conducted as a sensitivity analysis, including only participants who completed the study with full adherence to the protocol, to assess the robustness of the primary findings.

All statistical analyses will be conducted using IBM SPSS Statistics Version 31 or R 4.3.2 (R Foundation for Statistical Computing, Vienna, Austria). The level of statistical significance will be set at α = 0.05 for all primary analyses, with corresponding confidence intervals reported where applicable. Adjustment for multiple comparisons will be applied as appropriate, using either Bonferroni correction or false discovery rate (FDR).

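### Both mixed models omit a visit term although scans are paired within visits; if same-visit scans correlate, the primary interaction tests are conservative and the phase and olanzapine main-effect tests usually too liberal

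*Protocol article*

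**What the plan says.** The Statistical analysis section of the protocol article sets out two linear mixed models.

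- **Model 1** (hypothesis 1) uses placebo visits only: "analyses will be restricted to visits in which participants receive the oral PL". Its fixed effects are intranasal condition, phase and their interaction, and the interaction is the primary term. Its random part is: "Participant will be included as a random intercept, with age and BMI entered as covariates".
- **Model 2** uses all visits and adds oral condition with all interactions. The three-way interaction is the primary term. Its random part is: "Participants will be modeled as a random intercept, with age and BMI as covariates".

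Neither model has a visit or session term.

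The Study design section, with its Fig 2 legend, fixes the data structure:

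- Number of visits: "Each participant will undergo a total of four primary study visits, two per cycle phase (follicular and luteal")
- Spacing of those visits: "Study visits will take place 2–6 weeks apart to ensure specific menstrual phase across the four visits and adequate washout between conditions"
- Scans on the imaging day of a visit: "There will be two MRI scans on day 2, the first following administration of INP and the second following 160 IU of INI"
- Level at which the oral treatment changes: "All participants will receive oral PL at visit 1 and oral OLA at visit 2 of each cycle phase"

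**The concern.** This is a split-plot layout. Intranasal condition varies within a visit; phase and oral condition vary only between visits. The two scans of a visit share whatever is particular to that day, such as sleep, arousal, hormone level and scanner state, and the next visit is weeks away.

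A participant intercept alone makes all of a participant's scans equally correlated: four in Model 1, eight in Model 2. Day-level variation then goes into a single residual. The primary interactions are contrasts of within-visit differences, from which a visit effect cancels, yet they would be judged against a residual that contains it. Phase and olanzapine main effects carry the visit effect in full and would be judged against a residual that contains only part of it.

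At stake is power for the two named tests, in a study of 15 that relies on within-subject efficiency to justify its size. There is also a risk that a phase or olanzapine main effect read from the model output looks significant too often.

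**Working it through.** **Plan's own figure.** The article reports no formal power calculation, so there is none to reproduce.

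**Inputs from the article.** N = 15; two scans per visit; two visits per participant in Model 1 and four in Model 2; α = 0.05 (two-sided assumed); cited effects d 0.8 to 1.4.

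**Assumptions.**
- Let σ²v be the visit variance, σ²e the scan residual variance and w = σ²v/σ²e. The documents do not give w, so a range is shown.
- Data are complete and balanced. Age and BMI then do not affect within-participant contrasts.
- Insulin acts only at the follicular placebo visit, with standardised within-visit difference d_z = (0.8 + 1.4)/2 = 1.1. Reading the cited d as a d_z is itself an assumption.

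**Error variance of a contrast, in common units.**
- Within-visit contrasts (insulin, insulin × phase, the three-way term): σ²e
- Between-visit contrasts (phase, olanzapine, phase × olanzapine): σ²e + 2σ²v
- Pooled residual, Model 1 (one between-visit and two within-visit contrasts): σ²e + (2/3)σ²v
- Pooled residual, Model 2 (three between-visit and four within-visit contrasts): σ²e + (6/7)σ²v

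**Ratio of the planned SE to the correct SE.**
- Insulin × phase, Model 1: √(1 + 2w/3)
- Phase, Model 1: √[(1 + 2w/3)/(1 + 2w)]
- Three-way, Model 2: √(1 + 6w/7)
- Phase and olanzapine, Model 2: √[(1 + 6w/7)/(1 + 2w)]

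| w | Insulin × phase | Phase (Model 1) | Three-way | Phase, olanzapine (Model 2) |
|---|---|---|---|---|
| 0 | 1.00 | 1.00 | 1.00 | 1.00 |
| 0.1 | 1.03 | 0.94 | 1.04 | 0.95 |
| 0.25 | 1.08 | 0.88 | 1.10 | 0.90 |
| 0.5 | 1.15 | 0.82 | 1.20 | 0.85 |
| 1 | 1.29 | 0.75 | 1.36 | 0.79 |

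For example, at w = 1: √(1 + 2/3) = √1.667 = 1.29, and √(1.667/3) = 0.75.

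**Power benchmark.** The Model 1 interaction is a difference of two independent within-visit differences, so its d_z is 1.1/√2 = 0.78. That is the value at which a paired t-test with n = 15 has 80% power.

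**Simulated Model 1 results** (balanced data, no participant-by-insulin variance):

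| w | Insulin × phase power, plan | Power, paired contrast | Phase type I error, plan |
|---|---|---|---|
| 0 | 84% | 80% | 5% |
| 0.1 | 82% | 80% | 6% |
| 0.25 | 79% | 80% | 8% |
| 0.5 | 75% | 80% | 11% |
| 1 | 66% | 80% | 14% |

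The nominal 5% interaction test has true size of about 2.5% at w = 0.5 and 1.3% at w = 1. The plan's advantage at w = 0 comes from degrees of freedom: 3 × 14 = 42 for the pooled residual against 14 for the paired contrast. The two approaches break even near w = 0.2.

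**Model 2.** The same scenario gives the three-way contrast a d_z of 1.1/2 = 0.55. Simulated power is about 48%, 41% and 29% under the plan at w = 0.25, 0.5 and 1, against about 51% for the paired contrast. Type I error for olanzapine is about 8%, 10% and 12.5%.

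**Sensitivity.** With w about 0.1 and a participant-by-insulin variance of 0.5, type I error for phase falls to about 4.7%. The interaction test stays conservative (about 3%).

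**The case against.** The strongest reply is that the fault is conditional. No variance component or within-visit correlation is given, the planned model is correct at w = 0, and below about w = 0.2 it has slightly more power for the Model 1 interaction when participants do not differ in their insulin response. The larger losses come from w = 0.5 to 1, which nothing in the article establishes. This stands and limits the claim about size. It does not remove the mismatch: the article itself states the random part, and the stated part leaves out a level that the design contains.

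A reader might infer more than the documents support:

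- **False positive primary findings.** For both primary interactions the error runs the other way. The phase and olanzapine main effects are only model terms; the hypotheses concern insulin effects and their inhibition. Their inflation can also vanish, as the sensitivity case shows.
- **A wrong choice of maximum likelihood over REML.** The words "using the maximum likelihood estimation within the linear mixed" come from the sentence on missing data. They do not settle that choice, which commonly goes to the analysis plan. Read literally, maximum likelihood would shrink the Model 1 SE by √(42/45) = 0.966. That partly offsets the conservatism: planned power would be 81%, 77% and 69% at w = 0.25, 0.5 and 1.
- **An omitted random slope for intranasal condition.** Participants may differ in insulin response, but that is a separate question from the nesting of scans in visits and is no part of this error.

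**Conclusion.** The point holds in conditional form. Both stated models ignore the pairing of scans within visits. If w is above zero, the primary interactions are tested too conservatively, and the phase and olanzapine main effects usually too liberally.

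The effect on Model 1 power is negligible or slightly favourable up to about w = 0.25. It is a loss of about 5 points at w = 0.5 and 14 at w = 1. These figures assume n = 15, complete data, no participant-by-insulin variance and a within-visit d_z of 1.1 confined to the follicular placebo visit. Some visit variance is plausible for same-day scans separated by weeks from the next pair, but its size is unknown.

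This is a should-fix. It does not invalidate the primary tests, the study describes itself as exploratory, and the article reports recruitment as ongoing, so the model can be settled before analysis.

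**What to change.** Add a random intercept for visit within participant to both models, alongside the participant intercept. Equivalently, test the two primary interactions on the within-visit insulin-minus-placebo differences. With complete data, the Model 1 interaction can then be a paired t-test on each participant's follicular-minus-luteal difference, which is valid whatever the visit variance. State a small-sample degrees-of-freedom method. If phase or olanzapine main effects are reported, take them from the model with the visit term and label them as not primary.

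The change is one extra random term in each model. Its price is fewer error degrees of freedom, costing up to about 4 points of power in Model 1 (84% to 80%) if there is no visit variance. Specifying REML or a participant random slope for intranasal condition is optional and not needed to correct this point.

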## Objectives and hypotheses

In this study, we seek to address a significant gap in the literature by investigating 1) how brain insulin action differs in females according to their menstrual cycle phase, and 2) how a high metabolic liability agent such as OLA might interrupt these differential insulin effects. We have chosen to conduct this study in healthy volunteers to minimize confounding effects of psychiatric disorders on glucose metabolism [36]. OLA was selected as a representative antipsychotic due to its well-established metabolic liability [37]. An acute dosing paradigm (i.e., two days of dosing) is employed to avoid longer-term changes in adiposity [38]. thereby allowing for a more precise assessment of whether antipsychotics exert direct effects on brain insulin function.

Resting state functional activity and connectivity (rsFC) will be used as a neural signature of brain insulin action. We hypothesize that 1) INI, but not intranasal placebo (INP), will modulate resting state activity in the brain in females during the follicular phase of their menstrual cycle but not the luteal phase; 2) Oral OLA will inhibit all INI-induced effects, relative to oral placebo (PL) during the follicular phase. OLA will have no apparent effect in the luteal phase given pre-existing brain IR.

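### The only term named for hypothesis 2 is the three-way interaction, which tests phase specificity and does not by itself test follicular inhibition by olanzapine

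*Protocol article*

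**What the plan says.** The protocol article, under Objectives and hypotheses, gives hypothesis 2 in two sentences. The first is "Oral OLA will inhibit all INI-induced effects, relative to oral placebo (PL) during the follicular phase". The second is "OLA will have no apparent effect in the luteal phase given pre-existing brain IR".

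Under Statistical analysis, the model for this hypothesis opens with its purpose: "To test the effect of OLA within each phase, a second linear mixed effects model will be conducted including all visits". It has fixed effects for intranasal condition, oral condition and phase, with every interaction, and the random part is "Participants will be modeled as a random intercept, with age and BMI as covariates". The term chosen for inference is then given as "The primary term of interest is the intranasal condition x oral condition x menstrual phase interaction", explained as a test of whether OLA's modification of the INI effect differs between phases.

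The preceding paragraph, on the hypothesis 1 model, does name within-phase contrasts: "Planned simple effects will assess (i) the effect of INI vs. INP within each phase". The paragraph on the second model names none.

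On the data available, Study design says "each treatment is administered once during each menstrual cycle phase, resulting in participants receiving all conditions twice over the course of the study", which gives eight scans per participant, one per cell. The sample size is 15, chosen by precedent and without a power calculation. The same section cites Cohen's d of 0.8 to 1.4 from earlier INI imaging studies, and alpha is 0.05 for all primary analyses.

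**The concern.** The stated purpose of the second model is a within-phase question, and the first sentence of hypothesis 2 is a within-phase claim. The named term answers a between-phase question. A plan followed as written would therefore judge follicular inhibition by a quantity that can be zero when inhibition is complete, and non-zero when there is none.

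The main pharmacological question could then be answered wrongly in either direction. A true follicular blockade could be reported as unsupported because OLA also acts in the luteal phase, or because the three-way term is imprecise at N = 15. A significant three-way term could be reported as support when the follicular contrast shows nothing. If the follicular contrast is looked at only afterwards, it becomes a post-hoc choice.

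**Working it through.** **Inputs.** N = 15, alpha 0.05 and d = 0.8 to 1.4 come from Statistical analysis; eight cells with one scan each come from Study design; the model is as stated (random intercept, residual variance s²). Assumptions not in the document: two-sided testing, complete data, and d read as the paired effect (mean INI − INP difference divided by its SD, where INP is intranasal placebo and the SD is √2·s).

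**Plan's own figure.** N = 15 has no formula or power target, so there is nothing to reproduce. For reference, a paired t-test at d = 0.8 with n = 15 has 82.1% power. That is a simple INI versus INP comparison, not an interaction.

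**What each term is.** Let F be the follicular double difference, (INI − INP under OLA) − (INI − INP under oral placebo, PL), and L the same in the luteal phase. The follicular claim is about F. The three-way term is F − L.

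**Variances.**
- F combines four scans per participant: 4s²/n = 4s²/15 = 0.267s².
- F − L combines eight: 8s²/15 = 0.533s².
- The ratio is 2.00 whatever the random-intercept variance, because the intercept cancels.
- If F and L correlate within participants at ρ, the ratio is 2(1 − ρ): 1.5 at ρ = 0.25 and 1.0 at ρ = 0.5.

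**Power under the hypothesised pattern** (full follicular blockade, L = 0). Both terms then have expected size d·√2·s, so the noncentrality is d·√(15/2) = 2.74d for F and d·√(15/4) = 1.94d for the three-way term. Noncentral t is used with 14 df (participant-level contrasts) and 98 df (7 × 14, the mixed model):

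| d | F, 14 df | three-way, 14 df | F, 98 df | three-way, 98 df |
|---|---|---|---|---|
| 0.8 | 0.53 | 0.30 | 0.58 | 0.34 |
| 1.0 | 0.72 | 0.44 | 0.77 | 0.48 |
| 1.4 | 0.95 | 0.71 | 0.97 | 0.77 |

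Participants needed for 80% power, with mixed-model df: 25 against 50 at d = 0.8, 16 against 32 at d = 1.0, and 9 against 17 at d = 1.4.

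**Other patterns** (effect size d = 1.0, 98 df, chance of rejection):

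| True pattern | F | three-way |
|---|---|---|
| Equal blockade in both phases | 77% | 5% |
| Luteal effect half the follicular one | 77% | 16% |
| No follicular effect, luteal effect of the same size | 5% | 48% |

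The first row shows that a significant three-way term is not necessary for follicular inhibition. The third shows that it is not sufficient.

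**Luteal part.** With 14 df the 95% confidence interval for L has half-width t(0.975, 14)/√15 = 0.554 SD of L itself, which is 0.554 × √2 = 0.78 SD of a change score if the two change scores are uncorrelated. A true luteal effect of 0.5 SD of L would give p > 0.05 in 56% of trials.

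**The case against.** **The three-way term is relevant to hypothesis 2.** Taken together, its two sentences predict a difference between phases, and the three-way term tests that. This stands. A reader might infer that the named term does not test hypothesis 2 at all; the document does not support that. The term tests one part of the pattern and leaves the follicular part untested on its own.

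**The follicular contrast is more exposed to bias.** Under Study design, oral placebo always comes at the first visit of a phase and OLA at the second, and intranasal placebo always precedes INI. A constant visit effect cancels in INI − INP. A difference between visits in drift from scan 1 to scan 2 (habituation, drowsiness) does not cancel, and would look like an OLA effect. The three-way term removes such drift if it is common to both phases. This also stands, and it is a good reason to keep the three-way term.

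**The article is condensed, and the contrast can be estimated.** Both within-phase contrasts can be obtained from the model as specified, and a list of follow-up contrasts may sit elsewhere. So the absence of such a list is not the point. The point is that the article does fix a term for inference, and that term does not match the purpose given in the same paragraph.

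**Nothing says a luteal p > 0.05 will be read as no effect.** Correct. A reader might infer that rule from the luteal sentence of the hypothesis, but the document states no such rule and promises confidence intervals where applicable.

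**The study calls itself exploratory.** That word explains the missing power calculation. It does not remove the mismatch, since a primary term and an alpha are still set.

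**Conclusion.** The point holds as a mismatch between the model's stated purpose and its named term. The interaction tests phase specificity; it is neither necessary nor sufficient for follicular inhibition. This conclusion rests on the definition of the terms alone and needs no assumption about effect size or correlation.

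The size of the power loss does need assumptions. The factor of two in variance is exact for the stated random-intercept model with complete data, but should not be read as unconditional: the document gives no correlation between phase-specific contrasts, and at ρ = 0.5 the disadvantage disappears. The power figures further assume that the cited d is a paired effect and that the luteal effect is zero. No stated power target is contradicted.

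This should be fixed, but it does not invalidate the design or the model.

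**What to change.** In Statistical analysis, for the second model:

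1. Pre-specify the follicular intranasal × oral contrast, estimated from the same eight-cell model, as the test of the follicular-inhibition claim.
2. Keep the three-way interaction as the test of phase specificity, and require it before claiming that OLA's effect depends on phase.
3. Report the luteal intranasal × oral contrast with its confidence interval, and state that non-significance will not be taken as evidence of no effect.
4. State that the fixed order exposes the follicular contrast to visit-order differences in scan-1-to-scan-2 drift, which the three-way term removes only if they are common to both phases. Report the two together for that reason.

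The cost is two contrast statements and a few sentences. No new data, model or participants are needed. The article reports recruitment as ongoing, so the change can be made before analysis. The price is that the inhibition claim then rests on the contrast more open to order effects, which item 4 discloses but does not remove.

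### The per-protocol sensitivity analysis of hypothesis 1 drops women for events at olanzapine visits, although that hypothesis uses only the placebo visits (minor)

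*Protocol article*

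**What the plan says.** All of this is in the Protocol article.

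- **Per-protocol set (Statistical analysis).** The one sensitivity analysis named uses a per-protocol set, defined as "including only participants who completed the study with full adherence to the protocol, to assess the robustness of the primary findings". The rule is set by person, and no separate set is given for each hypothesis.
- **Primary set (same section).** The intention-to-treat analysis is described as "including all participants enrolled in the study who have completed at least one study visit", with missing data handled by maximum likelihood under missing at random.
- **Data for hypothesis 1 (same section).** "analyses will be restricted to visits in which participants receive the oral PL".
- **Data for the olanzapine question (same section).** "a second linear mixed effects model will be conducted including all visits".
- **Visits and their order.** The Fig 2 caption says "Each participant will undergo a total of four primary study visits, two per cycle phase (follicular and luteal"). The Study design section says "All participants will receive oral PL at visit 1 and oral OLA at visit 2 of each cycle phase".
- **Adherence.** The Study design section says "OLA levels will be measured to assess adherence". The Investigational products section adds the return of empty blister packs and spray administration in front of staff.

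**The concern.** The membership rule does not match the data that hypothesis 1 uses. Completing the study means completing four visits, and two of these contribute nothing to the hypothesis 1 model. A missed capsule or a withdrawal at an olanzapine visit leaves the placebo-visit scans as valid as before, yet it removes the woman from the check.

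Two things are at stake. The first is precision: in a trial of 15, each valid participant removed widens the interval noticeably. The second is interpretation. This is the only sensitivity analysis that the article names for the primary findings. If its hypothesis 1 estimate differed from the primary one, the cause could be poor adherence at placebo visits, which is relevant. It could also be the removal of women for what happened on olanzapine, which is not. The rule as written cannot separate the two.

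**Working it through.** The article gives no figure for the size of the per-protocol set, so there is nothing to reproduce. The check has a logical part and a sizing part.

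**1. The last visit is an olanzapine visit whichever phase comes first.** Each phase has two visits, placebo then olanzapine. The final visit of the study is the second visit of whichever phase ends last, so it is on olanzapine. This holds if one phase is finished before the other (placebo, olanzapine, placebo, olanzapine) and if the phases are interleaved (for example placebo, placebo, olanzapine, olanzapine). The article does not clearly state which applies.

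**2. Who is lost without need.**

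| Event | Hypothesis 1 data intact? | In per-protocol set as written? |
|---|---|---|
| Deviation at a placebo visit | No | No |
| Leaves before her second placebo visit | No | No |
| Both placebo visits adherent, deviation at an olanzapine visit | Yes | No |
| Both placebo visits adherent, leaves before the final olanzapine visit | Yes | No |

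Only the last two rows are avoidable losses.

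**3. Size of the avoidable loss.**

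Inputs from the article: planned N = 15 (Statistical analysis); 13 enrolled, 3 dropped out, 6 completed (Recruitment status and study timeline), so 13 − 3 − 6 = 4 were still active.

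Assumptions: 15 is total enrolment, dropouts are not replaced, and no one else leaves, so at most 15 − 3 = 12 complete. Each visit has an independent probability p of some deviation, the same at placebo and olanzapine visits. The article gives no p, so a range is shown.

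Expected number retained = 12 × (1 − p)^k, with k = 4 under the stated rule and k = 2 if only placebo visits count.

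| p | k = 4 | k = 2 | Difference |
|---|---|---|---|
| 5% | 12 × 0.8145 = 9.8 | 12 × 0.9025 = 10.8 | 1.1 |
| 10% | 12 × 0.6561 = 7.9 | 12 × 0.81 = 9.7 | 1.8 |
| 15% | 12 × 0.5220 = 6.3 | 12 × 0.7225 = 8.7 | 2.4 |

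For p of 5–10%, the avoidable loss is about one to two people. Anyone who left after her second placebo visit would add to it. Clustering of deviations within the same women would reduce it.

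**4. What that does to precision.** For a within-person contrast, the 95% half-width in SD units is t(0.975, n − 1)/√n. This gives 0.67 at n = 11, 0.72 at n = 10, and 2.365/√8 = 0.84 at n = 8. Going from 11 to 10 people widens the interval by about 6% (0.715/0.672). Going from 10 to 8 widens it by about 17% (0.836/0.715).

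**5. Selection on tolerance.** Step 3 uses the same p at every visit, so it models random loss and says nothing about selection. If the fraction q least tolerant of olanzapine were removed, and tolerance had correlation ρ with the hypothesis 1 contrast, the mean would shift by ρ·φ(c)/(1 − q) SD, where c is the normal quantile at q. With q = 3/13 to 3/9 (dropouts over all enrolled, or over those with a known outcome), the shift is 0 at ρ = 0, 0.08–0.11 SD at ρ = 0.2 and 0.20–0.27 SD at ρ = 0.5. Neither ρ nor the share of losses due to intolerance is in the article, and q here counts every dropout as an intolerant woman. This is a what-if range, not an estimate.

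**The case against.** The strongest reply is that this is one condensed sentence in a journal article, that detailed per-protocol rules normally sit in the full protocol or the analysis plan, and that a fully adherent completer set is a conventional choice giving both hypotheses one common population. Part of this stands. A completer set is defensible for the olanzapine model, whose three-way interaction draws on all four visits. But the article does not leave the rule open: it states a person-level criterion, and that criterion does not fit its own restriction of the hypothesis 1 data.

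It is also fair to reply that the primary inference is untouched and the study describes itself as exploratory. Both are true, and they keep the point minor.

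Four stronger readings are tempting, and the documents do not support them:

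- **That the set demonstrably selects olanzapine-tolerant women.** The definition permits this, and the Limitations section anticipates transient sedation. But the article gives neither reasons nor visits for the three dropouts, the withdrawal reasons under Study participants do not name intolerance, and poor adherence need not reflect it.
- **That the set fails as a check on missing at random.** The article never gives it that purpose; it speaks only of robustness.
- **That the rule costs the power lost between n = 15 and n = 10 to 12.** For d = 0.8 that would be 0.82 falling to 0.62–0.71. But the comparison charges all dropout to the rule, whereas women who leave before their second placebo visit cannot supply the full contrast under any rule.
- **That the olanzapine model needs a visit-level set.** Such a set keeps more data but leaves incomplete sequences that again rely on missing at random. It is a trade-off, not the correction of an error.

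**Conclusion.** The point holds for hypothesis 1 and is minor. As written, the per-protocol rule removes women with two valid placebo visits because of deviation or dropout at olanzapine visits.

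The avoidable loss is about one to two people out of 12. That rests on an assumed independent 5–10% deviation rate per visit, no replacement of dropouts and no further dropout. Selection on olanzapine tolerance is possible, but its size cannot be estimated from the article; if tolerance is unrelated to the hypothesis 1 contrast, the cost is precision only. The primary intention-to-treat result for hypothesis 1 is not affected.

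**What to change.** Add one sentence to the Statistical analysis section: for hypothesis 1, the per-protocol set consists of participants whose two oral-placebo visits were both completed per protocol, regardless of events at olanzapine visits. The stated completer set may stay for the olanzapine model.

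No new data are needed, because blister packs and staff-administered sprays already document adherence visit by visit. Recruitment was still open when the article was submitted. The wording should be settled before the data are analysed.

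The downside is that the two hypotheses will have different per-protocol populations. The report should give the number in each and the reasons for exclusion.
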